**A TECHNOLOGY-SUPPORTED PE COURSE TO INCREASE THE PA LEVELS OF UNIVERSITY STUDENTS: RCT**

## STATEMENT OF COMPLIANCE FOR NON DRUG OR DEVICE CLINICAL TRIALS

This document is a protocol for a clinical research study. The study will be conducted in compliance with all stipulations of this protocol, the conditions of ethics committee approval, the [NHMRC National Statement on Ethical Conduct in Human Research](#) (as updated) and the [Handbook for Good Clinical Research Practice \(GCP\)](#). [The Therapeutic Goods Act has adopted ICH Guideline for Good Clinical Practice.](#)

## 2. SYNOPSIS

|                               |                                                                                                                                                                                                                                                                                                                                                                                                                                                                                                                                                                                                                                                                                                                                                                                                       |
|-------------------------------|-------------------------------------------------------------------------------------------------------------------------------------------------------------------------------------------------------------------------------------------------------------------------------------------------------------------------------------------------------------------------------------------------------------------------------------------------------------------------------------------------------------------------------------------------------------------------------------------------------------------------------------------------------------------------------------------------------------------------------------------------------------------------------------------------------|
| TITLE                  | A technology-supported physical education course to increase the physical activity levels of university students: A randomised controlled trial                                                                                                                                                                                                                                                                                                                                                                                                                                                                                                                                                                                                                                                |
| OBJECTIVES             | A prototype LMS, incorporated within a mobile phone app, was specifically designed and built to support a physical education course learning process at an Indonesian university. The app aimed to increase university students' physical activity levels, knowledge, and motivation. The prototype was tested and modified in 2021 with a small sample size. The randomised controlled trial (RCT) will recruit a larger sample size with the aim to test and evaluate the modified prototype Learning Management System (LMS) and mobile app. All students will receive the same content. Students in the intervention group will have access to the modified prototype mobile app that incorporates the LMS. This will enable them to access course content, feedback via their smartphone. |
| PRIMARY HYPOTHESIS     | A technology-supported physical education course intervention will increase university student's physical activity levels, knowledge and motivation more effectively than non-technology-supported physical education courses.                                                                                                                                                                                                                                                                                                                                                                                                                                                                                                                                                                 |
| DESIGN                 | This is a two-arm parallel, randomised controlled trial of a technology-supported physical education course intervention for students enrolled in an elective unit of study.                                                                                                                                                                                                                                                                                                                                                                                                                                                                                                                                                                                                                   |
| BLINDING/MASKING       | The lecturers (n=6) will not be blinded as those randomly assigned to the intervention group (n=3) will be involved in professional development before they implement the intervention.                                                                                                                                                                                                                                                                                                                                                                                                                                                                                                                                                                                                        |
| OUTCOMES               | Primary outcome: Difference in students' physical activity levels, knowledge and motivation at post-test (at the completion of a 16-week semester) compared with the control group.
Secondary outcome: Student's experience and enjoyment of the technology-supported physical education course.                                                                                                                                                                                                                                                                                                                                                                                                                                                                                           |
| STUDY DURATION         | 16 weeks.                                                                                                                                                                                                                                                                                                                                                                                                                                                                                                                                                                                                                                                                                                                                                                                      |
| INTERVENTION/S         | A 16-week physical education course incorporating the modified prototype Learning Management System (LMS) and mobile app.                                                                                                                                                                                                                                                                                                                                                                                                                                                                                                                                                                                                                                                                      |
| NUMBER OF PARTICIPANTS | 6 lecturers (a) n=3 will be assigned to the intervention group, (b) n=3 will be assigned to the control group.
n=300 students will be randomised 1:1 to either an intervention arm (a) n=150 a technology-supported physical education group or (b) n=150 usual physical education.                                                                                                                                                                                                                                                                                                                                                                                                                                                                                                        |

|                                |                                                                                                                                                                                                                                                                                                  |
|--------------------------------|--------------------------------------------------------------------------------------------------------------------------------------------------------------------------------------------------------------------------------------------------------------------------------------------------|
| POPULATION              | University students who enrol physical education course at Universitas Pendidikan Indonesia, Bandung, Indonesia                                                                                                                                                                           |
| SELECTION AND ENROLMENT | Students will be included in the RCT if they meet the following inclusion criteria: 1) students enrolled in the elective physical education course with a lecturer who will participate in the RCT study; 2) voluntarily participate in the RCT study; and 3) owns an android smartphone. |

### 3. RATIONALE / BACKGROUND

Interventions focusing on increasing physical activity levels among various age groups from early childhood to the elderly have been growing over the last five years. These studies have suggested that targeting physical activity at different time points across the lifespan is essential, especially when there is a transition related to educational events. For example, the transition from preschool to primary school, from primary to high school, and from high school to college or university. Yet, the last opportunity to intervene before adulthood is the transition into post-secondary studies. Therefore, this period is ultimately the most important for establishing lifelong actions such as personal, psychosocial, and movement behaviours for those who have not yet established them. Physical activity tends to significantly decrease when graduating from high school and enrolling in universities and among first-year university students, with 80% of university students not meeting physical activity recommendations during this transition. These studies show that promoting physical activity opportunities for university students is essential.

Providing university courses that improve student's physical activity levels may be a viable option, as universities can provide students with access to a range of sports facilities, highly educated facilitators, and appropriate technologies. However, establishing and maintaining quality university courses at the university level has been a concern. As such, a guideline developed in the US and China suggests that administration/support, assessment, instructional strategies, professionalism, learning environment, program staffing, and curriculum are essential facets that promote quality. Previous studies also suggest that providing strategies for administration and directors, modelling the development and support for course instructors, and utilising technology can be viable strategies for increasing the quality of university courses' that aim to improve the physical activity levels of university students.

There are various factors influence physical activity behaviour in young adults. Gaining knowledge of physical activity is considered one of the principal determining factors of physical activity in university-age students. Study involving 258 adults in Hong Kong found that physical activity knowledge had a positive correlation with levels of physical activity, with this correlation strongest among the university student participants. This finding is also supported by a Chinese cross-sectional study recruiting 9826 university students. This study found that knowledge of physical activity guidelines was correlated with higher physical activity levels. Thus, physical activity knowledge should be considered as one of the learning outcomes of physical education courses in a university setting.

Another important factor that is widely known to be associated with physical activity is motivation. Exercise motivation plays an important role in long-term physical activity behaviour. Systematic reviews examine relationships between motivation and physical activity and examine the effects of physical activity interventions underpinned by motivational principles show that motivation significantly increases physical activity levels.

Furthermore, a cross-sectional study involving 1079 participants age 24±9 years showed that motivation for physical activity and exercise is associated with frequency, intensity, and duration of exercise. This finding is also supported by an observational study using a web-based survey involving 320 wearable activity monitor users. This study found that motivational regulation was correlated with moderate to vigorous physical activity. Hence, having motivational outcomes as part of a physical education course in university settings should also be considered.

Research focusing on technologies that promote university students' physical activity levels is gaining more attention. The most common strategy utilised in previous studies has been internet websites. Most reported studies utilising internet websites have been successful in increasing physical activity levels. Another common form of technology utilised to enhance university students' physical activity levels are wearable devices. These have ranged from pedometers to activity trackers (Misfit, Jawbone UP, Polar M400, Fitbit, and MyWellness Key). Two of four (50%) studies that utilised a pedometer successfully increased participants mean steps per day. Two of five (40%) studies using activity trackers also increased student's physical activity levels. Social media, smartphone applications or mobile apps have also become a technology form that has been used to enhance the physical activity levels of university students. Three of seven (43%) studies using this technology have also successfully increased students' physical activity levels. However, it is important to highlight that most of the studies utilising technology that aim to increase student's physical activity levels in university settings were non-course-based interventions.

The randomised controlled trial (RCT) aims to test and evaluate the modified prototype with a larger sample size. The prototype of technology-supported physical education includes lecturer website-based learning management system integrated with student's mobile app. This prototype is specifically design and build to support physical education course learning process at university setting aims to increase university students' physical activity levels.

#### 4. AIMS / OBJECTIVES / HYPOTHESES

**Aims and Objectives:** A prototype LMS, incorporated within a mobile phone app, was specifically designed and built to support a physical education course's learning processes at an Indonesian university. The app aims to increase university students' physical activity levels, knowledge, and motivation. The prototype was tested and modified in 2021 with small sample size. The randomised controlled trial (RCT) will recruit a larger sample size with the aim to test and evaluate the modified prototype Learning Management System (LMS) and mobile app. Students in the intervention group will have access to the modified prototype mobile app that incorporates the LMS. This will enable them to access course content, feedback via their smartphone. Students in the control group will receive the same content using standard teaching methods.

**Hypothesis:** A technology-supported physical education course intervention will increase university student's physical activity levels, knowledge and motivation more effectively than a non-technology-supported physical education courses..

#### 5. PARTICIPATING SITES

This study is being conducted in one state university (Universitas Pendidikan Indonesia) in Bandung, Indonesia. The physical education course is offered to first-year or second-year

students as a requirement or as an elective course. This university has seven faculties: 1) Faculty of Education; 2) Faculty of Science and Math Education; 3) Faculty of Social Science Education; 4) Faculty of Language, and Literature Education; 5) Faculty of Technology and Vocational Education; 6) Faculty of Sport and Health Education; and 7) Faculty of Arts and Design Education. Students from the Faculty of Sport and Health Education are not required to take a physical education course, while students from the Faculty of Art and Design are required to enrol in the physical education course. For students from the other five faculties, they are allowed to choose between the physical education course or a variety of Arts courses. This organisation will divide students into three groups which will be appropriate for this study: 1) students who are required to enrol in the physical education course; 2) students who choose to enrol in the physical education course; and 3) students who do not choose to enrol and participate in a physical education course.

## 6. RESEARCH PLAN / STUDY DESIGN

### 6.1 Type of study

This is a two-arm parallel, randomised controlled trial of a technology-supported physical education course intervention for students enrolled in an elective unit of study. The six lecturers who agree to participate will be randomly assigned to the intervention or control group. Students who enrol randomly by the University system with the participated lecturers of physical education course will be invited to participate in the study. The intervention lecturers will have lecturer training and implement the 16-week technology-supported physical education course intervention for one semester. The Primary outcome is to examine the difference in students' physical activity levels, knowledge and motivation at post-test (at the completion of a 16-week semester) compared with the control group. The secondary outcome is students' experience and enjoyment of the technology-supported physical education course intervention.

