### 6.2 Sample size including power calculation

The sample size calculation is based on the difference in change in the primary outcome (physical activity) from pre- to post-intervention in both group (intervention and control group). Based on previous studies on technology-based physical activity interventions in university students, mean effect sizes of around  $d = 0.5$  are expected in analyses. To detect such intervention effects in two-sided significance testing ( $\alpha = .05$ ) with a power of 80%, a sample size of 128 participants is required. Taking into account an expected study drop-out of about 20%, 150 participants must be included in the study and participants response rate of about 50%, hence, 300 students (six classes of physical education course) will be invited.

Number of Participants

N=6 physical education course lecturers

(a) n=3 will be assigned to the intervention group,

(b) n=3 will be assigned to the control group.

n=300 students will be randomised 1:1 to either an intervention arm

(a) n=150 a technology-supported physical education course (intervention group)

(b) n=150 non-technology-supported physical education course (control group).

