#### **6.4 Recruitment and selection of participants\***

The randomised controlled trial will include six lecturers and six classes (20 to 50 students each class or  $n=300$ ). There are two recruitment processes in this RCT including the lecturer and students. The lecturer will be included in the RCT if he/she meets the following inclusion criteria: 1) run two classes of the physical education course; 2) willing to take part in lecturer training before the physical education course class begins; and 3) willing to invite their students to take part in the pilot study. The chief investigator A/[name] will be sending the recruitment to applicable members of staff at Universitas Pendidikan Indonesia especially lecturers who run the elective physical education course.

The chief investigator A/[name] will be sending the recruitment letter to students enrolled in a physical education course via the participating lecturers (and consenting). Participation in this RCT is voluntary, and all participants will be given Participant Information Statements and invited to sign a Participant Consent Form to participate. Participation or non-participation in this study will not affect students' scores in physical education courses. The number of students in each class varies from 20-50 students. Students will be included in the RCT if they meet the following inclusion criteria: 1) students enrolled in a physical education course with a lecturer who will participate in the pilot study; 2) voluntarily participate in the RCT; and 3) owns an android smartphone. The six lecturers who agree to participate will be randomly assigned to intervention or control. Participation in this RCT is voluntary, and all lecturers and students will be given Participant Information Statements and be invited to sign a Participant Consent Form to participate.

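### The protocol says 300 students are randomised 150 to 150, but the unit it randomises is six lecturers, whose classes of 20 to 50 give 60 to 150 invited students per arm

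*Protocol*

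**What the plan says.** Two descriptions of the allocation stand side by side.

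- **Lecturers are randomised.** Section 6.1: "The six lecturers who agree to participate will be randomly assigned to the intervention or control group". Sections 6.4 and 6.6 repeat this. The synopsis and section 6.2 fix the split at three lecturers per arm ("n=3 will be assigned to the intervention group", and the same for control). Students come into the trial through their lecturer: "Students who enrol randomly by the University system with the participated lecturers" are then asked to take part (6.1).
- **Students are randomised.** Section 6.2: "n=300 students will be randomised 1:1 to either an intervention arm", with 150 in each arm. The synopsis row on number of participants says the same.

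Section 6.2 also gives 300 as the number to be invited, of whom 150 are to be included after an expected response of about 50%.

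On classes, section 6.4 says "The randomised controlled trial will include six lecturers and six classes" and "The number of students in each class varies from 20-50 students". Its lecturer criteria, however, require that each lecturer "run two classes of the physical education course".

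No pairing, stratification or other balancing of the lecturer draw is described.

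**The concern.** The protocol's own statement of what is randomised, and how many fall in each arm, is wrong as written. A reader of the synopsis would take this for an individually randomised trial of 300 students. The procedure in 6.1, 6.4 and 6.6 is a cluster allocation of six lecturers with about 150 participants. The unit determines how the trial is described, registered and analysed. The arm sizes determine what recruitment is judged against. A later analysis plan cannot settle this, because the allocation is made before any analysis.

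A smaller matter follows. With six units of unequal size, the draw itself decides how unequal the arms are, and the protocol describes nothing that limits this.

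**Working it through.** **1. The plan's own figure.** Inputs from 6.2: d = 0.5, two-sided alpha 0.05, power 80%. The two-sample t-test needs 63.8, so 64 per arm, or 128 in total. This reproduces the stated 128, but for individually randomised students. The step from included to invited is 150 / 0.5 = 300, which also matches.

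**2. What the lecturer draw delivers.** Inputs: three lecturers per arm (6.2) and classes of 20 to 50 (6.4).

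| Reading of 6.4 | Invited per arm | Invited in total |
|---|---|---|
| One class per lecturer (six classes) | 3 × 20 = 60 to 3 × 50 = 150 | 120 to 300 |
| Two classes per lecturer (twelve classes) | 6 × 20 = 120 to 6 × 50 = 300 | 240 to 600 |

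With six classes, 150 versus 150 is the upper limit and needs 50 students in every class. At the stated 50% response, an arm would have 60 × 0.5 = 30 to 150 × 0.5 = 75 participants. With twelve classes, a total of 300 needs an average of 300 / 12 = 25 per class.

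**3. How unequal the arms could be.** The actual class sizes are not given, so assume 20, 26, 32, 38, 44 and 50 (total 210). There are C(6,3) = 20 ways to split six lecturers three and three:

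| Arm totals | Ratio | Allocations |
|---|---|---|
| 102 v 108 | 1.06 | 6 |
| 96 v 114 | 1.19 | 6 |
| 90 v 120 | 1.33 | 4 |
| 84 v 126 | 1.50 | 2 |
| 78 v 132 | 1.69 | 2 |

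So 12 of 20 stay within 1.25:1, 8 exceed it, and 2 exceed 1.5:1.

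**4. What that inequality costs.** Student-level efficiency relative to equal arms is 4ab/(a+b)².
- At 78 v 132: 4 × 78 × 132 / 210² = 0.93.
- At 1.25:1: 4 × 1.25 / 2.25² = 0.99.
- At the extreme of 60 v 150: 4 × 60 × 150 / 210² = 0.82.

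**5. What pairing would gain.** In a simulation with six class sizes drawn uniformly from 20 to 50 (assumption), the median difference between arms is 15 students and the 90th percentile 36. Pairing lecturers by class size before the draw lowers these to 7 and 17.

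**6. What balancing on size cannot do.** The protocol gives no intraclass correlation (ICC), so a range of 0 to 0.10 is assumed. With three classes per arm, the 95% range of a chance arm difference from class and lecturer effects is ±1.96 × √(2 × ICC / 3):
- ICC 0.01: ±0.16 SD
- ICC 0.02: ±0.23 SD
- ICC 0.05: ±0.36 SD
- ICC 0.10: ±0.51 SD

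With 150 / 6 = 25 participants per class, a class-level t-test on 4 degrees of freedom has non-centrality 0.5 / √(2(ICC + (1 − ICC)/25)/3). Its power is 64% at ICC 0, 48% at 0.02 and 25% at 0.10.

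**The case against.** The best defence is that 150 versus 150 is a nominal target: six classes of 50 make 300, the lecturer split is 3:3, and 1:1 is shorthand for that. Section 6.1 adds that the university system enrols students with lecturers at random. Part of this stands. The total of 300 fits six full classes, and unequal arms alone cost little. But the shorthand names the wrong unit. Random enrolment with a lecturer is done by the university and is not described as a 1:1 allocation to arms. Section 6.4 says that class sizes vary, and 6.2 calls the 300 invited.

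Some stronger readings are tempting, and the protocol does not support them.

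- **Classes differ by faculty, and the difference could line up with arm.** If two of six classes shared a trait, both would fall in one arm in 8 of 20 allocations. With an assumed 0.3 SD difference, the arm contrast would shift by (2/3) × 0.3 = 0.2 SD. But section 5 lists faculties for the university, not for classes, and the random enrolment in 6.1 points towards mixed classes. The pre-test covariate in 6.3 would also remove part of any stable difference.
- **Chance class differences could swamp the effect.** A chance difference as large as the planned 0.5 SD is plausible only near ICC 0.10, a value that the protocol does not give.
- **The draw is unrestricted.** That would be an inference from silence, and the fixed 3:3 split is itself a restriction.

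A practical objection also stands. Section 11 puts lecturer training in the second half of August and student recruitment in September. Only intervention lecturers are trained, so the draw must come by August. Nothing shows that class sizes are known by then.

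**Conclusion.** The contradiction is established from the text alone: lecturers are randomised, students are not, and 300 is the number invited. The stated 150 per arm does not follow from the described procedure. With one class per lecturer it is the top of a range of 60 to 150 invited. The range depends on reading 6.4 as six classes. If each lecturer brings two, it becomes 120 to 300, which is a further reason to settle that conflict.

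The absence of a balancing step is a secondary point. The allocation counts rest on assumed class sizes. The likely loss from unequal arms is small, so restricted randomisation is a modest improvement and not a cure. The protocol does not support a claim that the comparison is invalidated by unequal arms or by faculty mix.

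**What to change.** **Needed, at the cost of a few sentences.** In the synopsis and section 6.2:
- Name the lecturer, with his or her class, as the randomised unit.
- Replace the statement of 300 students randomised 1:1 with 150 per arm by three lecturers per arm, about 300 students invited and about 150 included, with the expected range per arm.
- Reconcile six classes with the criterion of two classes per lecturer in 6.4, and check that the total of 300 still fits. Six classes reach it only at 50 each, twelve at an average of 25.
- Allow in the range for the rule in 6.5, under which another class is invited if fewer than 30 students agree, since it can change the numbers.

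**Worthwhile if class sizes are known before the draw.** In 6.1, 6.4 and 6.6, either pair lecturers by class size and randomise within pairs, or list the 20 three-versus-three allocations, keep those within a set size ratio such as 1.25:1, and draw one at random. Balance on faculty only if class lists show that classes differ. Each added constraint shrinks the set of allocations, and with six units very few may remain.

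The costs are that class sizes must be obtained before the draw and that fewer allocations are possible: 12 of 20 in the example, or 2³ = 8 under pairing. Equal class lists will not guarantee equal participants at a response of about 50%. The small number of clusters is a separate problem, which only the sample size and the number of lecturers can address.
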